## Adverse events

An adverse event (AE) is defined as any untoward medical occurrence in a patient or clinical investigation subject administered a pharmaceutical product and which does not necessarily have a causal relationship with this treatment. An adverse event (AE) can therefore be any unfavourable and unintended sign (including an abnormal laboratory finding), symptom, or disease temporally associated with the use of a medicinal (investigational) product, whether or not related to the medicinal (investigational) product.

## Solicited AEs

No solicited AEs will be sought in this study.

## Grading of AEs

All AEs will be assessed for severity by the investigator. Inherent in this assessment is the medical and clinical consideration of all information surrounding the event including any medical intervention required. Each event will be assigned one of the following categories: mild, moderate, severe, or life-threatening. The criteria below may be used for any symptom not included in the grading scale. Any grade 4 (life-threatening) AE must be reported as an SAE.

The CRF for AEs will reflect only the highest severity for continuous days an event occurred.

• Grade 1 (Mild): Does not interfere with routine activities, minimal level of discomfort

• Grade 2 (Moderate): Interferes with routine activities, moderate level of discomfort

• Grade 3 (Severe): Unable to perform routine activities, significant level of discomfort

• Grade 4 (Potentially life-threatening): Hospitalization or ER visit for potentially

life-threatening event

If a subject is evaluated in an emergency room for nonlife threatening illness or symptoms (i.e., visits emergency department on weekend for mild problems because the physician’s office is closed), the information from that visit will be reviewed and severity of the adverse event will be assessed according to the subject’s clinical signs and symptoms.

As defined by the ICH guideline for GCP, the term “severe” is often used to describe intensity (severity) of a specific event (as in mild, moderate, or severe myocardial infarction); the event itself however, may be of relatively minor medical significance (such as severe headache). This is not the same as “serious”, which is based on subject/event outcome or action criteria usually associated with events that pose a threat to a subject’s life or functioning. Seriousness (not severity) serves as a guide for defining regulatory reporting obligations.

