### Clinical aspects

*L. loa* infection may present with several distinct clinical patterns ranging from asymptomatic infection to severe disease. From a parasitological point of view loiasis can be classified in occult loiasis – in the absence of microfilaraemia – and loiasis with peripheral microfilaria. The infection most commonly causes chronic skin itching, arthralgia, transient localized angioedema (callabar swelling) and sometimes an adult worm can be seen traversing the conjunctiva of an infected individual. Importantly, most of these *L. loa* associated symptoms and signs appear to be related to the adult worm and not to the microfilaria. Very rarely, infected individuals can develop renal and cardiac problems, presumably in part immune-mediated. Chronic eosinophilia in infected individuals has been associated with endo-myocardial fibrosis and related heart failure ([5](#_ENREF_5)), although in general (transient) eosinophilia is more often observed in travellers with incidental exposure than in endemic populations ([6](#_ENREF_6), [7](#_ENREF_7)). Spontaneous encephalitis has been described in some heavily infected patients ([8](#_ENREF_8)).

However, because for the vast majority of infected people symptoms are considered as benign and due to potentially life-threatening complications of inappropriate treatment, infected individuals usually do not receive curative treatment in regions of high endemicity.

Due to its globally-limited geographic distribution, the fact that it mainly affects poor rural populations and that *Loa loa* is not (even) included on the WHO’s list of neglected tropical diseases, relatively little is still known about this disease. Indeed, despite its endemic presence in Africa and the magnitude of the population infected or at risk of the disease, loiasis drew little medical, scientific or political attention until the implementation of mass drug administration (MDA) for lymphatic filariasis (LF) and onchocerciasis in the region and the associated risks experienced by *L. loa*-infected individuals became apparent (see Treatment options, below).

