## Study visits

### Screening

Potential participants will be informed again about the study aims, design, in- & exclusion criteria and procedures. If still willing to participate, subjects will be asked to sign written informed consent. Thereafter, a full medical history and concomitant medication will be recorded and a physical examination will be performed. Blood will be drawn for laboratory safety parameters (haematology, biochemistry, serology) and to confirm microfilarial levels and to exclude pregnancy in female subjects. In addition a single stool sample and urine sample will be collected to assess
helminth infection (since we will be treating with albendazole which
will also have an effect on many helminths), which could affect
tolerability and influence non-specific symptoms such as pruritus. Indeed helminth infection also affect immune response, therefore it will be necessary to know the subject helminth status.

Any abnormal findings that result in exclusion from the study and/or require treatment will be communicated to the subject; for any treatment required beyond that which can be provided directly by the study team, subjects will be referred to other healthcare providers as appropriate.

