## Assessment of AE relatedness

The investigator must assign a relationship of each AE to the receipt of study medication. The investigator will use clinical judgment in conjunction with the assessment of a plausible biologic mechanism, a temporal relationship between the onset of the event in relation to receipt of the investigational product(s), and identification of possible alternate aetiologies including underlying disease, concurrent illness or concomitant medications. The following guidelines should be used by investigators to assess the relationship of an AE to study medication:

• Not related: No relationship to investigational product. Applies to those events for which evidence exists that there is an alternate aetiology.

• Unlikely: Likely unrelated to the investigational product. Likely to be related to factors other than investigational product, but cannot be ruled out with certainty.

• Possible: An association between the event and the administration of investigational product cannot be ruled out. There is a reasonable temporal association, but there may also be an alternative etiology such as the subject’s clinical status or underlying factors including other therapy.

• Probable: There is a high degree of certainty that a relationship to the investigational product exists. There is a reasonable temporal association, and the event cannot be explained by known characteristics of the subject’s clinical state or factors including other therapy.

• Definite: An association exists between the receipt of investigational product and the event. An association to other factors has been ruled out

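### One highest-grade record per continuous AE, with timing judged from onset, can lose the date and drug phase of a symptom that worsens after treatment

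*Protocol*

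**What the plan says.** Recording rule, section 7.4 (Grading of AEs): "The CRF for AEs will reflect only the highest severity for continuous days an event occurred". A symptom that runs without a break therefore carries one grade, its worst.

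Relatedness, section 7.5: "The investigator will use clinical judgment in conjunction with the assessment of a plausible biologic mechanism", together with "a temporal relationship between the onset of the event in relation to receipt of the investigational product(s" and possible alternate aetiologies, among them underlying disease. The category Possible applies where "An association between the event and the administration of investigational product cannot be ruled out", with a reasonable temporal association.

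Solicitation, section 7.3: "No solicited AEs will be sought in this study".

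Background symptoms, section 3.1.2: "The infection most commonly causes chronic skin itching, arthralgia, transient localized angioedema". The Screening part of section 6.2 explains that stool and urine are examined because helminth infection could affect "tolerability and influence non-specific symptoms such as pruritus".

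Endpoints, section 4.3.2: the primary safety endpoint is any grade 3 AE or SAE, whatever its relatedness. A second safety endpoint takes grade 1-2 AEs, but only those at least possibly related to study therapy. Both run from the start of each arm to 6 months.

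The protocol has no rule that an increase in grade starts a new AE, is dated separately, or is judged again against a later drug. The AE definition in section 7.2 does not mention worsening of a condition already present.

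**The concern.** The symptoms by which tolerability would be noticed are largely those the infection itself causes. Some participants may have itching or joint pain at DT0, or still have it when the second treatment starts. For them the informative event after a drug is an increase in grade, not a new onset. The recording rule keeps the size of that increase but provides no date for it, and the relatedness rule looks to the earlier date.

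Two things are at stake. The first is the endpoint for possibly related grade 1-2 AEs, where the relatedness rating decides whether an event counts. The second is the ability to say which drug an event followed. Section 7.1.1 places the risk of treatment reactions mainly with DEC and ivermectin, regards albendazole as generally free of them, and calls the ivermectin risk below 4000 mf/mL almost negligible. That statement can be checked in arm 4 only if a worsening after ivermectin carries a date after ivermectin.

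**Working it through.** **Numbers exposed.** Section 5.2 asks for 8 evaluable participants per treatment arm and allows one third loss: 8 / (1 − 1/3) = 12 per arm, and 6 + 3 × 12 = 42 in total. Both stated figures reproduce. Arms 3 and 4 are due a second treatment: 12 + 12 = 24. All 36 participants in arms 2-4 (3 × 12) receive a first albendazole course.

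**Following a worsening symptom through the rules.**

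| Symptom begins | Worsens | Grade 1-2 endpoint | Primary safety endpoint | Date and phase |
|---|---|---|---|---|
| Before DT0 | To grade 2 after albendazole | Can drop out: onset precedes the drug and underlying disease is a listed alternative cause | Not relevant | Can be lost |
| Before DT0 | To grade 3 after a drug | Not relevant | Relatedness is ignored; whether an event with onset before the arm began counts is not stated | Can be lost |
| Between DT0 and DRT0 | To grade 2 after second treatment | Onset already follows study drug, so the event can still count for the arm | Not relevant | Can be placed in the first course |
| Between DT0 and DRT0 | To grade 3 after second treatment | Not relevant | Counted: highest grade kept, relatedness ignored | Can be placed in the first course |

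So the possible loss from an endpoint lies with symptoms already present at DT0. For later onsets the loss is of date and drug. Section 7.5 asks for the relation to study medication in general, so the relatedness rating does not by itself restore the drug.

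**Is there a baseline that could repair this?** Section 6.2 provides a medical history and examination at screening. Under section 4.4 recruitment may take about 2 months before any arm starts, and arms 3 and 4 start after arms 1 and 2, so that history can be old by DT0. The descriptions of DT0 and DRT0 list blood draws and dosing but no grading of current symptoms.

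**Size, on assumed inputs.** The protocol gives no symptom rates. Let q be the share of arm 4 with an ongoing symptom at re-treatment and w the share of those whose symptom worsens afterwards. The expected number of worsenings that carry an earlier onset is n × q × w. The chance of at least one is 1 − (1 − qw)^n, if participants are independent. With q = 20-60% and w = 10-50%:

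- n = 12: 12 × 0.2 × 0.1 = 0.24, up to 12 × 0.6 × 0.5 = 3.6. Chance of at least one: 1 − 0.98^12 = 22%, up to 1 − 0.70^12 = 99%.
- n = 8: 0.16 to 2.4. Chance of at least one: 15% to 94%.

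These are events whose date could be wrong, not events lost from an endpoint. The range is too wide to serve as a magnitude.

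**The case against.** The strongest reply has five parts.

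1. **Onset is only one input.** Section 7.5 also weighs clinical judgement, mechanism and other causes, and Possible has a low threshold. A flare the day after ivermectin has obvious timing, and an investigator may well rate it related. This stands. A reader might infer that such worsening is always attributed to before the drug; the text allows that but does not require it.
2. **Grade 3 events survive.** The primary safety endpoint ignores relatedness and section 7.4 keeps the worst grade. This stands for AEs that begin after DT0. A reader might infer that severe worsening is generally undercounted, or that an arm's grade 3 proportion shifts; a misdated event leaves that proportion unchanged.
3. **Symptoms before DT0 may be medical history, not AEs.** Section 7.2 speaks of subjects who have been given a product. A later worsening could then be a fresh AE with a proper date. This is a fair reading, but the protocol does not say so, and two investigators could record the same worsening differently.
4. **No endpoint is defined by treatment phase, and the CRF and SOPs are not shown.** Both are true. The safety objective concerns whole regimens, and the CRF may hold more dates than section 7.4 implies. But section 7.4 prescribes what the CRF shows, and if it is followed literally, no analysis can recover a date that was not collected.
5. **Unsolicited AE collection is a legitimate choice in a descriptive pilot.** This stands. AEs are recorded daily in the first week of each treatment round and at every follow-up visit. A reader might take section 7.3 as part of the attribution fault, or as leaving detection wholly to spontaneous reports. The documents support neither: solicitation concerns how completely symptoms are picked up, and the protocol does not say how participants are questioned.

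**Conclusion.** The point holds as a gap in the recording rules. Sections 7.4 and 7.5 together allow a worsening after a drug to carry the date of an earlier, milder onset. A grade 1-2 worsening of a symptom present before DT0 can drop out of the endpoint for possibly related AEs. A grade 3 worsening of an AE that began after DT0 is counted, but its date and its link to albendazole or ivermectin can be lost. The phase problem concerns the 24 participants of arms 3 and 4; the baseline problem concerns any treated participant with a symptom at DT0.

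The conclusion assumes that section 7.4 is applied as written and that the unseen CRF adds no date of worsening. How many events are affected depends on symptom rates the protocol does not give, so no shift in any arm's proportion is claimed. This is a cheap improvement, worth making because the missing information cannot be reconstructed at analysis.

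**What to change.** Record the grade of every ongoing symptom at DT0 in all arms and at DRT0 in arms 3 and 4. Replace the sentence in section 7.4 with:

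> Any increase in grade after DT0, or after DRT0, opens a new AE record with its own start date, grade and relatedness to the most recent study drug.

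The cost is a change of CRF wording and a few more AE records, all at existing visits. Because one participant can then have several records for one symptom, the safety tables should count participants as well as records. In arm 1, where no study drug is given, the same grading and dating apply without the relatedness item.

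A short fixed list of symptoms, asked identically in all four arms, is optional. It would make detection more even in an open-label trial, but it is not needed to correct attribution.

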## Assessment of AE relatedness

The investigator must assign a relationship of each AE to the receipt of study medication. The investigator will use clinical judgment in conjunction with the assessment of a plausible biologic mechanism, a temporal relationship between the onset of the event in relation to receipt of the investigational product(s), and identification of possible alternate aetiologies including underlying disease, concurrent illness or concomitant medications. The following guidelines should be used by investigators to assess the relationship of an AE to study medication:

• Not related: No relationship to investigational product. Applies to those events for which evidence exists that there is an alternate aetiology.

• Unlikely: Likely unrelated to the investigational product. Likely to be related to factors other than investigational product, but cannot be ruled out with certainty.

• Possible: An association between the event and the administration of investigational product cannot be ruled out. There is a reasonable temporal association, but there may also be an alternative etiology such as the subject’s clinical status or underlying factors including other therapy.

• Probable: There is a high degree of certainty that a relationship to the investigational product exists. There is a reasonable temporal association, and the event cannot be explained by known characteristics of the subject’s clinical state or factors including other therapy.

• Definite: An association exists between the receipt of investigational product and the event. An association to other factors has been ruled out

## SAEs

An AE is considered “serious” if it results in any of the following outcomes:

• Death

• A life-threatening situation

• Inpatient hospitalization or prolongation of existing hospitalization

• Persistent or significant disability/incapacity defined as a “substantial disruption of the ability to conduct normal life functions”

• Congenital anomaly/birth defect (in the offspring of a subject)

An AE or suspected adverse reaction is considered “life-threatening” if its occurrence places the patient or subject at immediate risk of death. It does not include an adverse event or suspected adverse reaction that, had it occurred in a more severe form, might have caused death.

Important medical events that may not result in death, be life-threatening, or require hospitalization may be considered serious when, based upon appropriate medical judgment, they may jeopardize the patient or subject and may require medical or surgical intervention to prevent one of the outcomes listed in this definition. Examples of such medical events include allergic bronchospasm requiring intensive treatment in an emergency room or at home, blood dyscrasias or convulsions that do not result in inpatient hospitalization, or the development of drug dependency or drug abuse.

SAEs must be reported to the safety monitor and responsible ethical committee within 24 hours.

SAEs will be collected and recorded from all participants throughout the trial, from the moment of inclusion until the end of follow-up (i.e. 6 month after commencement of each study arm).

## Oversight

A safety monitor, i.e. a clinician with experience in clinical trials who is permanently on site and is independent of the clinical trial team, will oversee participant safety. He/she may recommend halting or stopping the trial.

# Ethics

## Governing principles

This study will be performed in accordance with the current revision of the Declaration of Helsinki and the latest versions of the ICH guidelines for Good Clinical Practice (GCP) and guidelines for Good Clinical Laboratory Practice (GCLP).

## Informed consent

Written, informed consent will be obtained from all study subjects prior to inclusion, as described above. This consent may be withdrawn by the study subject at any time, without being required to provide a reason.

## Risks and benefits to study subjects

Risks to study subjects are discussed in section 7.1 Risks. Benefits include provision of symptomatic treatment for signs and symptoms of loiasis to subjects in all arms throughout the study. Note that the anti-filarial treatment provided to subjects in arms 2-4 cannot be defined as a benefit, since the (long-term) parasitological and clinical efficacy of albendazole and ivermectin in Loa-endemic populations remains to be clarified.

## Ethical review

This trial will be submitted for ethical review to the Institutional Review Board (Comité d’Ethique institutionel, CEI) of the Centre de Recherches Médicales de Lambaréné (CERMEL), which is registered with the Registration Office for Human Research Protections (OHRP) with the numbers: IORG0007336 / IRB00008812.

# Data and Quality issues

## Data management

All study subjects will allocated a unique pseudonymised study code at screening; only investigators, safety monitor, IRB and Sponsor will have access to these records. Data will be recorded on paper case record forms (CRFs) using these study codes and will be entered in an electronic database for further analysis. All laboratory samples will also be labelled, processed and stored until end of analysis but no longer than 5 years using these study codes. Data analysis will be performed following a predefined statistical analysis plan.

## Quality control and assurance

All study procedures, whether clinical or laboratory-based will be performed in accordance with the current versions of CERMEL’s relevant Standard Operation Procedures (SOPs). CERMEL also has an overall Quality Assurance programme in operation. An external monitor will perform regular monitoring to check that the trial is conducted, and that data are recorded, analysed & accurately reported, according to study protocols, relevant SOPs and in compliance with ICH GCP. Internal audits are also performed of laboratory activities and in addition CERMEL’s laboratories are enrolled in External Quality Assurance programmes.

